#### Randomization and allocation concealment

The random numbers will be generated using SPSS 26.0 software. An independent research assistant not involved in recruitment or evaluation will place the random numbers sequentially into sealed, opaque envelopes. Each envelope is individually labeled with a unique consecutive serial number. Eligible patients will be randomly assigned to the verum acupuncture group and the sham acupuncture control group at a 1:1 ratio. The flowchart is shown in Figure 1.

**Figure 1 fig1:**
[figure not shown]
Flowchart of trial process.

#### Blinding

During the process of treatment, patients will wear opaque eye masks for all interventions to prevent visual identification of treatment type (verum acupuncture vs. sham acupuncture). Patients will complete a blinding assessment during the Post-Acupuncture Resting State phase. Acupuncturists will be unblinded to group assignment, and identical procedures will be maintained for both interventions. The evaluators will conduct a blind assessment to reduce expectation bias and observer bias in data collection. Statistical analyses will be conducted by a statistician blinded to group allocation.

### Intervention

#### Verum acupuncture group

Acupuncture will be performed at the Quchi acupoint (LI11) bilaterally using the following standardized protocol: Sterile, single-use acupuncture needles measuring 0.30 mm in diameter and 40 mm in length will be used. The needle will be inserted to a depth of 0.5 inches (approximately 1.25 cm). After achieving DeQi sensation with the primary needle, an auxiliary needle (0.18 mm in diameter and 13 mm in length) will be inserted adjacent to the primary needle to allow for the application of electrical stimulation. Electrical stimulation will be applied to both the primary needle and auxiliary needle for 5 min (20 Hz continuous wave, current intensity 1–5 mA). Acupoint locations are depicted in Figure 2.

**Figure 2 fig2:**
[figure not shown]
Locations of acupoints and non-acupoints. NA, non-acupoint.

#### Sham acupuncture group

The sham acupuncture procedure will be administered at non-acupoint location, specifically 1.0 cm inferior and lateral to LI11 bilaterally. Two blunt-tip needles (0.30 mm in diameter and 40 mm in length) will be applied: one at the designated non-acupoint (sham primary acupoint) and an auxiliary needle placed 0.5 cm adjacent to it (sham auxiliary point). All procedural protocols (needle retention time: 5 min, and electrode placement) will match the verum acupuncture group except for the use of a blunt-tip needle that does not penetrate the skin and the absence of electrical output. Acupoint locations are displayed in Figure 2.

### Outcomes

The assessment will be conducted before and after the treatment, and the assessment time points are presented in Table 1.

**Table 1 tab1:** Data collection schedule for clinical assessments.

Research phase	Pre-acupuncture resting state	Intervention period	Post-acupuncture resting state
Timepoint	5 min before needle insertion	During the needle retention period	5 min immediately after needle withdrawal
Medical history			
Signed informed consent	✓		
Inclusion/exclusion criteria	✓		
Demographic & baseline data			
Demographic questionnaire	✓		
Past medical history	✓		
Concomitant treatments	✓		
Psychometric scales			
Self-Rating Depression Scale	✓		
Pittsburgh Sleep Quality Index	✓		
Generalized Anxiety Disorder-7	✓		
Clinical assessments			
Degree of itch Relief		✓	
Itch intensity	✓	✓	✓
Immediate comfort level		✓	
Treatment expectancy	✓		
Treatment credibility scale		✓	
Deqi intensity scale		✓	
Trial evaluation			
Adverse events record			✓
Physician/Patient Global Assessment			✓
Blinding assessment			✓

#### Primary outcomes

The primary outcome was defined as the change of the itch NRS score, calculated by subtracting the post-intervention score from the baseline score. The intensity of itch will be evaluated using the NRS. The NRS is a patient-reported instrument in which subjects rate their subjective itch intensity on a numerical scale anchored at 0 (“no itch”) and 10 (“worst imaginable itch”). Measurements will be conducted at pre-acupuncture resting state, intervention period, and post-acupuncture resting state.

#### Secondary outcomes

##### Degree of itch relief

The degree of itch relief will be assessed immediately following each acupuncture treatment using a 5-point scale ranging from −2 to 2, where −2 indicates “significantly worsened,” −1 indicates “mildly worsened,” 0 indicates “no relief, 1 indicates “mildly relieved,” and 2 indicates “significantly relieved.”

##### DeQi intensity scale

The Chinese Modified Massachusetts General Hospital Acupuncture Sensation Scale(C-MASS) will be employed to evaluate the intensity of diverse needling sensations experienced during acupuncture manipulation. The deqi sensations include: deep aching, sharp pain, pressure, heaviness, distension, tingling, numbness, dull pain, warmth, coldness, and pulsation. The intensity of the deqi sensation is rated on a scale of 0 to 10, 0 indicates no sensation, 1 to 3 is mild, 4 to 6 is moderate, 7 to 9 is severe, and 10 is intolerable intensity. The assessment will be conducted subsequently, immediately upon completion of the acupuncture treatment session.

### fNIRS data acquisition

In this study, a 49-channel fNIRS system (NirSmartII-3000A, NirScan, Danyang Huichuang Medical Equipment Co., Ltd., China) will be used to monitor hemodynamic changes in the prefrontal cortex and motor areas. The sampling rate is 11 Hz, and the appropriate wavelengths for the NIR laser are 730 nm and 850 nm, respectively. The fNIRS detection cap consists of 23 light sources and 15 detectors, with a spacing of 3 cm between the light sources. The channels in the right hemisphere are CH1-CH25; the channels in the left hemisphere are CH26-CH49. The positioning information of the channel, light source and detector is shown in Figure 3.

**Figure 3 fig3:**
[figure not shown]
The fNIRS system distribution map.

#### fNIRS task

The fNIRS data will be continuously acquired from participants in a seated position across three consecutive 5-min epochs: (1) pre-acupuncture resting state (5 min before needle insertion), (2) intervention period (during 5-min needle retention), and (3) post-acupuncture resting state (5 min immediately after needle withdrawal). In this study, the term “fNIRS task” refers specifically to the intervention period. Throughout all three phases, participants must remain still and rest with their eyes closed, refraining from speech and minimizing head movement (Figure 4).

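### Itch, blinding and other ratings are scheduled inside fNIRS epochs that must be silent, still and eyes-closed, and the timing of the post-treatment primary NRS is not fixed

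*Protocol article*

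**What the plan says.** The fNIRS task section of the protocol article states that data are "continuously acquired from participants in a seated position across three consecutive 5-min epochs": before insertion, during needle retention and after withdrawal. It then sets the behaviour required of participants: "Throughout all three phases, participants must remain still and rest with their eyes closed, refraining from speech and minimizing head movement".

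Other sections place ratings in the same phases, under the same names:

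- Primary outcomes, on the itch NRS: "Measurements will be conducted at pre-acupuncture resting state, intervention period, and post-acupuncture resting state".
- Blinding: "Patients will complete a blinding assessment during the Post-Acupuncture Resting State phase". The same section has patients wear opaque eye masks during the interventions.
- Outcomes, Table 1: the column headed "During the needle retention period" is ticked for degree of relief, itch intensity, comfort, credibility and deqi. The column headed "5 min immediately after needle withdrawal" is ticked for itch intensity, adverse events, global assessment and blinding.

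For three of these ratings the text gives a different time from Table 1:

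- Relief: "The degree of itch relief will be assessed immediately following each acupuncture treatment using a 5-point scale".
- Deqi: "The assessment will be conducted subsequently, immediately upon completion of the acupuncture treatment session".
- Credibility: the Expectation and credibility section puts it after the final treatment session.

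**The concern.** A participant who is masked, silent and motionless cannot fill in a form or speak a score. Either the rating is given and the recording condition is broken, or the condition is kept and the rating moves to a time that the protocol does not name.

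Two things are at stake.

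- **Imaging.** The optodes cover the prefrontal cortex and motor areas, and the hypothesis concerns the medial prefrontal, orbitofrontal and premotor cortex. Judging a sensation, speaking and moving can engage those regions. The planned spline interpolation is aimed at motion artefact. It would not remove real cortical activity evoked by the act of rating.
- **Primary outcome.** The change score needs one post-intervention NRS. The post phase lasts 5 minutes, as long as the stimulation itself, and nothing says where in it the score is taken. In a trial of an immediate effect, a rating at needle withdrawal and one 5 minutes later are different measurements.

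**Working it through.** The plan gives no figure for the time taken by ratings, so there is nothing to reproduce. The check compares the timing statements and then sizes the overlap.

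**Step 1: timing, rating by rating.**

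| Rating | Table 1 | Text | Inside a recorded epoch? |
|---|---|---|---|
| Itch NRS (primary) | all three columns | all three named phases | yes, on both |
| Blinding assessment | post column | during the post phase | yes, on both |
| Relief | retention | straight after treatment | retention by the table, start of the post epoch by the text |
| Deqi | retention | straight after treatment | as for relief |
| Credibility | retention | after the final session | retention by the table, possibly outside all epochs by the text |
| Comfort | retention | no time found in the text | retention, on the table alone |

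The first two rows do not depend on how Table 1 is read, because running text alone puts them in conflict with the fNIRS task section. The relief, deqi and credibility rows show a second conflict, between table and text.

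**Step 2: is there a gap?** The epochs are described as consecutive and the acquisition as continuous. No pause, rating window, button press or similar device is mentioned. Moving relief and deqi from the table's slot to the text's slot shifts them from one recorded epoch to the start of the next.

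**Step 3: size in the retention epoch.** Inputs:

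- Epoch length: 5 min × 60 = 300 s (fNIRS task section).
- Deqi items: 11 sensations (DeQi intensity scale section).
- Time per item: not in the documents; 5 to 10 s is assumed.

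Share = items × seconds per item ÷ 300.

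- Table 1 taken literally: 11 deqi + NRS + relief + comfort + credibility = 15 items. 15 × 5 = 75 s and 15 × 10 = 150 s, or 25% to 50%.
- Text preferred where it differs: relief, credibility and the 11 deqi items (13 in all) leave the epoch, so NRS and comfort remain. 2 × 5 = 10 s and 2 × 10 = 20 s, or 3.3% to 6.7%.

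On the second reading, the 11 deqi items and relief (12 items) do not disappear. If rated at once after withdrawal while recording continues, they take 12 × 5 = 60 s to 12 × 10 = 120 s, or 20% to 40% of the 300 s post epoch.

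**The case against.** The best defence is that Table 1's columns are phase labels and not literal windows. Consent, eligibility, history and three psychometric scales sit under the heading for the 5 minutes before insertion, and they cannot all be done in 5 silent minutes. The sentence introducing the table speaks only of assessment before and after treatment. Insertion, obtaining deqi and connecting the electrodes must also take some time between the first two epochs. Figure 4, the timing diagram, is not shown and may mark rating points. A journal article may also leave minute-level procedure to a fuller document.

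Much of this stands. Ratings at epoch boundaries may well be intended, so the documents do not show that the study is unworkable. The defence does not remove the conflict in the running text, where the NRS and the blinding assessment are assigned to the very phases declared silent. Nor does it settle the disagreement between Table 1 and the text.

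Three stronger readings are tempting and are not supported:

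- **That rating at the chair undoes assessor blinding.** The needle sets differ between arms, but no section places an evaluator in view of them, and the NRS is patient-reported.
- **That the artefact differs by arm and so could mimic a treatment effect.** Verum participants might have more sensations to report, but this is conjecture. The deqi scale is a fixed list rated 0 to 10, so the number of ratings is equal in both arms.
- **That a quarter to a half of the intervention recording is lost.** That is the top of the range. It counts 13 items that the text places after treatment.

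**Conclusion.** The inconsistency is real and should be fixed. The recording conditions in the fNIRS task section cannot be met together with the rating times in the Primary outcomes and Blinding sections and in Table 1, and Table 1 contradicts the text for relief, deqi and credibility. The consequences are unplanned speech, movement and evaluative activity in recordings of prefrontal and motor cortex, and a primary post-treatment score without a fixed time.

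The share of the retention epoch affected is about 3% to 7% if only NRS and comfort are rated there, and up to 25% to 50% if Table 1 is literal. Both ranges rest on the assumed 5 to 10 s per item. The conclusion also rests on the visible text, since Figure 4 could narrow the gap. No claim is made that blinding fails or that the verum–sham comparison is biased in a known direction.

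**What to change.** Reconcile the Blinding section, Table 1, the Primary outcomes, Degree of itch relief, DeQi intensity scale and fNIRS task sections, and the Expectation and credibility section, so that no rating falls inside an analysed recording segment:

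- Take NRS ratings at marked epoch boundaries, and exclude the marked intervals from the activation and connectivity analyses.
- State one fixed time after needle withdrawal for the primary post NRS, identical in both arms. The choice defines the immediate effect being measured, so the authors should make it explicitly.
- Collect deqi, relief, comfort, credibility, blinding and global assessments after recording ends.
- Separate recording periods from rating points in Table 1, and make Figure 4 agree.

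The cost is a revised table, edits to several short sections and one or two minutes more per visit. Deqi, relief and comfort would be rated after a short recall delay, which is the same for both arms.

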**Figure 4 fig4:**
[figure not shown]
Diagrams of experimental timing.

#### Data preprocessing of fNIRS

Preprocessing will be performed using the NirSpark system (Danyang Huichuang Medical Equipment Co., Ltd., China). First, channel quality check will be conducted. Second, raw light intensity signals will be converted to optical density (OD) units. Third, motion artifacts will then be corrected using spline interpolation. Fourth, the processed OD data will then be filtered to attenuate physiological noise. Finally, HbO concentration changes will be derived from the filtered data using the modified Beer–Lambert law.

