Neuroimaging modalities have been widely used to elucidate central mechanisms underlying itch, providing critical insights into cortical and subcortical processing of pruriceptive signals (23, 24). A functional magnetic resonance imaging (fMRI) study found that the functional connectivity of the right orbitofrontal cortex (OFC), medial prefrontal cortex, and premotor cortex in patients with chronic spontaneous urticaria was more deactivated than in healthy individuals (25). To investigate the mechanisms underlying itch sensation, Li et al. used near-infrared spectroscopy to monitor the dynamic changes of cortical oxygenated hemoglobin (HbO) and deoxygenated hemoglobin (HbR) concentrations in healthy subjects during histamine-induced itch, and the results demonstrated that multiple channels corresponding to Brodmann areas in the frontal cortex were activated (26).

Functional neuroimaging has greatly advanced our knowledge of itch-related brain activity, yet most studies rely on fMRI, which is costly, less tolerant to movement, and unsuitable for real-time monitoring during acupuncture. In contrast, functional near-infrared spectroscopy (fNIRS) provides a non-invasive, motion-tolerant, and temporally sensitive method for monitoring dynamic cortical hemodynamic changes during treatment (27, 28). This technique offers real-time monitoring, high time resolution and simple operation (29), and demonstrates robustness against motion interference and the ability to capture reliable data even during spontaneous itch (30).

Therefore, based on prior evidence (22, 25), we hypothesize that acupuncture’s immediate antipruritic effect correlates with modulation of cortical regions involved in itch processing, particularly the mPFC, OFC, and premotor cortex, which can be captured in real-time by fNIRS. The term “immediate effect” refers to the rapid, short-term modulation of symptoms observed shortly after a single acupuncture intervention. Thus, this study aims to characterize acupuncture’s immediate effect and corresponding cortical response using fNIRS technology.

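### The fNIRS plan names HbO as its only derived signal and describes no HbR check or systemic correction, so a blood-flow response to verum-only stimulation could be read as cortical activation

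*Protocol article*

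**What the plan says.** All references are to the protocol article.

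- **Data preprocessing of fNIRS** sets out five steps: channel check, conversion to optical density, spline motion correction, filtering against physiological noise (type and band not given), and conversion to concentration by the modified Beer–Lambert law. The last step reads "Finally, HbO concentration changes will be derived from the filtered data". HbR is not named.
- **fNIRS data acquisition** records two wavelengths ("wavelengths for the NIR laser are 730 nm and 850 nm") on 49 channels. It describes the cap as having "23 light sources and 15 detectors, with a spacing of 3 cm between the light sources". That is the only spacing given, and no short-separation channel is described.
- **Verum acupuncture group** has penetrating needles and current at 20 Hz, 1–5 mA, for 5 min. **Sham acupuncture group** has blunt needles that do not break the skin, at a neighbouring site, with "the absence of electrical output".
- **fNIRS task** has three consecutive 5-min epochs: rest, stimulation, rest.
- **Activation analysis** and **Functional connectivity** leave the model, thresholds and connectivity metric to be settled in light of the data. **Statistical analysis** compares activation and connectivity between the two arms with a two-sample t-test.
- The **Introduction** describes an earlier near-infrared itch study in healthy subjects as monitoring "cortical oxygenated hemoglobin (HbO) and deoxygenated hemoglobin (HbR) concentrations".

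**The concern.** The fNIRS contrast is meant to support a statement about cortical mechanism. The light also passes through scalp, so the HbO signal can carry changes in superficial and systemic blood flow. Noise of that kind that is unrelated to treatment is balanced by randomisation. A response provoked by penetration and current is not, because it follows from the allocation itself and falls on one side of the comparison.

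At stake is the interpretation of the imaging result. A verum-minus-sham difference in HbO might be reported as prefrontal or premotor activation when part of it is systemic, and the plan as described contains no step that would alert the reader.

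**Working it through.** The plan gives no figure on this point, so there is none to reproduce. The check sets the sections side by side and adds short algebra.

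**1. HbR is already in the data.** For each channel, the modified Beer–Lambert law gives, at wavelength λ,

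ΔOD(λ) = [ε_HbO(λ)·ΔHbO + ε_HbR(λ)·ΔHbR] × path length(λ).

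Two wavelengths (730 and 850 nm) give two equations in two unknowns. Solving for ΔHbO gives ΔHbR in the same inversion. No new recording is needed.

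**2. What the arm contrast estimates.** Write the sustained HbO response in an arm as C + S, where C is cortical and S is systemic or scalp. The arm difference is

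(C_verum − C_sham) + (S_verum − S_sham).

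The second bracket is zero only if the systemic response is the same in both arms. Penetration and current differ by design, so the plan gives no reason to assume this. The document has no data on S, so the systemic share of any observed difference is unknown.

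**3. What the filter can do.** The record lasts 3 × 5 min = 900 s, with one stimulation block of 300 s and no repeated blocks. A response sustained over that block lies at roughly 1/900 = 0.0011 Hz to 1/300 = 0.0033 Hz. If the cortical and systemic responses share that time course, a linear filter multiplies both by the same factor k:

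k·(C_verum − C_sham) + k·(S_verum − S_sham).

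The systemic share does not depend on k. A high-pass cutoff well above this band removes most of both; one below it keeps both. Filtering can reduce cardiac and respiratory oscillation, but whatever band is chosen it cannot tell these two sustained responses apart. This step assumes that the time courses match; different onset shapes would give a filter or model some leverage.

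**4. Connectivity.** Suppose each channel carries its own fluctuation with variance σ² and a shared systemic fluctuation with variance g², all independent. The correlation between two channels due to the shared part alone is g² / (g² + σ²), which rises with g². If g² is larger in verum, correlations are higher in verum without any neural coupling. This needs a shared component that varies during the epoch; a constant shift would not do it. The article does not say which epoch supplies the connectivity contrast.

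**5. What HbR adds.** As a working assumption from general fNIRS practice, cortical activation is expected to show HbO up with HbR down, whereas a systemic flow or volume change need not. The direction of the HbR arm difference is therefore informative but not decisive. If the true HbR difference were zero, symmetric noise would give the opposite sign about half the time. That is too weak for a pass/fail rule, though it is still useful when the estimate is shown with its uncertainty.

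**6. What does not change.** The sample size section rests on itch NRS scores (2.86 ± 1.07 against 2.00 ± 0.58). Deriving HbR alters neither that calculation nor the primary outcome.

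**The case against.** The strongest defence is that this is a condensed article. Naming HbO as the output does not forbid HbR, and the full protocol or analysis plan may include it along with systemic-noise handling. That tempers the point but does not remove it: the article leaves the activation model and connectivity metric open, yet its step list ends affirmatively in HbO.

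Several stronger readings are tempting, and the document does not support them:

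- *That systemic and cortical signals cannot be separated because only HbO is derived.* A noise filter is planned, the two-wavelength recordings allow HbR to be computed later, and HbR would itself separate the sources only in part. The absence of any described short-separation channel or systemic regressor matters at least as much.
- *That a systemic difference between the arms is established.* The document gives no heart-rate, blood-pressure or scalp-flow data. The mechanism is plausible; its size is assumed.
- *That sham participants have no DeQi.* The sham section states non-penetration and absence of current, and DeQi is an assessed outcome. Only those two contrasts, plus needle site, can be relied on.
- *That the cited near-infrared study used HbR to rule out systemic effects.* The Introduction says only that both signals were monitored.
- *That connectivity is inflated across all channel pairs in verum.* The epoch is not specified, and no current runs in the post-withdrawal rest.

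It is also fair to say that the Discussion calls the study a pilot that will not explore neural mechanisms comprehensively. The Abstract is more assertive: it expects the findings to provide a neurobiological basis for the effect.

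**Conclusion.** The point holds as a minor, inexpensive improvement. The plan names HbO as its only derived signal and describes no HbR check, short-separation channel or systemic regressor, while the compared arms differ in penetration and current. A sustained systemic or scalp response to that difference could be read as cortical activation or connectivity, and the unspecified filter cannot distinguish it from an equally sustained cortical response.

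The size cannot be computed from the document. The conclusion assumes that such a response may occur and may differ by arm, that its time course resembles the cortical one, and that no fuller document already provides the check. It concerns the interpretation of the imaging contrasts only.

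**What to change.** 1. In the final preprocessing step, derive HbR together with HbO.
2. Keep HbO as the tested signal, and report the arm difference for both HbO and HbR with its uncertainty.
3. State before the data are seen that an HbO difference without an opposite-direction HbR change will be described as possibly systemic. Use this as an interpretive check, not as a gate that decides whether a region counts as activated.
4. Add a prespecified sensitivity analysis of activation and connectivity with the all-channel mean removed.

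The timing matters because the activation section leaves the model and thresholds to be chosen partly from data quality; a check adopted afterwards would not be prespecified.

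The cost is some extra analysis of data already recorded, with no new hardware, participants or visits. HbR is noisier than HbO, and removing the all-channel mean may also remove true widespread activation, which is why it belongs in a sensitivity analysis only. Some mechanistic claims will have to be worded more cautiously, and even then HbR will not fully separate the two sources.
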